## Abstract

**Background::**

Insomnia and hypertension are diseases with a high prevalence and a known association with each other. Sihogayonggolmoryeo-tang (SYM) is an herbal medicine traditionally used for the treatment of insomnia disorder concurrent with hypertension. However, no scientific clinical evidence exists supporting the effects of SYM on these disorders. This study aims to explore the feasibility, effectiveness, and safety of SYM for the treatment of insomnia disorder with concurrent prehypertension or stage 1 hypertension.

**Methods::**

A prospective, randomized, wait-list controlled, parallel, pilot clinical trial has been designed for a study to be conducted in Daejeon, Republic of Korea. Thirty insomnia disorder patients with prehypertension or stage 1 hypertension will be randomly assigned to a SYM or wait-list group at a 1:1 ratio. The SYM group will be administered SYM granules twice a day for 4 weeks and followed-up for 2 weeks while the wait-list group will not receive SYM granules. All participants in both groups will be given brochures with instructions for maintaining sleep hygiene and lifestyle modifications to reduce hypertension. Data will be collected at baseline and at 2, 4, and 6 weeks after allocation. The primary outcome is the Insomnia Severity Index score at 4 weeks post-treatment. The secondary outcomes will consist of the Pittsburgh Sleep Quality Index, sleep diary, systolic and diastolic blood pressure, brachial-ankle pulse wave velocity, ankle-brachial index, atherosclerosis biomarkers, the Hospital Anxiety and Depression Scale, the 5-level EuroQol-5 dimensions, and the Patient Global Impression of Change. Adverse events and laboratory test results will be monitored to assess the safety. Data will be recorded in electronic case report forms and analyzed using SPSS Statistics, Version 24.0.

**Discussion::**

This is the first clinical trial to explore the effectiveness and safety of SYM for the treatment of insomnia disorder concurrent with prehypertension or stage 1 hypertension. The results of this study can form the foundation for a future multicenter, large-scale, confirmatory clinical trial.

**Trial registration::**

Clinical Research Information Service, KCT0005001 (registered on May 8, 2020).

## Introduction

1

According to the 5th edition of the Diagnosis and Statistical Manual of Mental Disorders (DSM-5), insomnia disorder is a quantitative or qualitative sleep disorder, with symptoms including difficulty initiating or maintaining sleep, early awakening, and having sleep difficulties at least 3 times a week for a period of 3 months or longer.^[1]^ The prevalence of insomnia disorder is reported to be 10% to 30% worldwide and as high as 50% to 60% in some cases.^[2]^ Particularly, in the Republic of Korea, according to the disease statistics data from the Korea Health Insurance Review and Assessment Service, the number of patients treated for insomnia has increased continuously from 461,790 in 2014 to 597,529 in 2018.^[3]^ Insomnia not only reduces the health-related quality of life for individuals but also increases the risk of depression, suicide, high blood pressure, and cardiovascular disease.^[4]^ Currently, various pharmacological interventions and cognitive behavioral therapy are being used to treat insomnia; however, their effects on insomnia-associated medical conditions are uncertain. In particular, insomnia is associated with hypertension, and adults with hypertension have a reported 1.5 to 3.18 times higher risk of insomnia than those without hypertension.^[5–8]^ For this reason, treatment of hypertension is considered an ideal secondary target for the treatment of insomnia in primary care settings. Recently, studies on the improvement of blood pressure with cognitive behavioral therapy, which is the primary treatment option for insomnia, have also been conducted.^[9]^

Herbal medicine is an intervention that has been used for centuries in East Asian countries. Several studies have confirmed the effectiveness and safety of herbal medicine for the treatment of insomnia and hypertension.^[10,11]^ In particular, herbal medicine refers to a natural product formulation containing a plurality of active ingredients that act on a plurality of targets and has attracted attention as a promising candidate capable of overcoming the limitations of conventional synthetic drugs with a single active ingredient.^[12]^ Recently, a systematic review of the efficacy and safety of herbal medicine treatment for elderly insomnia patients with hypertension suggested promising possibilities for herbal medicine treatment in improving insomnia, lowering blood pressure, and solving mental health problems such as anxiety and depression.^[13]^

Sihogayonggolmoryeo-tang (SYM; Saikokaryukotsuboreito in Japanese, Chai-Hu-Jia-Long-Gu-Mu-Li-Tang in Chinese) is an herbal prescription comprised of 11 herbs, specifically *Bupleuri Radix, Fossilia Ossis Mastodi, Ostreae Testa, Scutellariae Radix, Cinnamomi Ramulus, Poria Sclerotium, Zingiberis Rhizoma Recens, Zizyphi Fructus, Rhei Radix et Rhizoma, Pinelliae Tuber,* and *Ginseng Radix*. It is frequently used for the treatment of insomnia in East Asia,^[14,15]^ and experimental studies have shown that it can improve sleep disorders by reducing excitability in animal models.^[16]^ The blood pressure of patients with primary hypertension was reported to decrease significantly in 95.98% of cases when SYM was administered.^[17]^ In addition, when SYM combined with antihypertensives was administered to hypertensive patients with depression, both depression and hypertension were significantly improved compared with the results when only antihypertensives were administered.^[18]^ Thus, based on the properties of multiple targets and multiple active ingredients, SYM may affect not only insomnia but also hypertension at the same time and may reduce the complications caused by these disorders. In particular, considering that antihypertensive medications are not recommended in the prehypertensive stage and lifestyle modification is recommended before antihypertensive medications in the first stage of hypertension,^[19,20]^ SYM administration may not only improve sleep quality but also slow the progression of hypertension. However, no study has evaluated the effects of SYM on insomnia disorder concurrent with prehypertension or stage 1 hypertension. Therefore, the aim of this study is to explore the feasibility, preliminary effectiveness, and safety of SYM for the treatment of insomnia disorder with prehypertension or stage 1 hypertension.

## Methods/design

2

### Trial design

2.1

A prospective, randomized, wait-list controlled, parallel, pilot clinical trial will be performed at the Daejeon Korean Medicine Hospital of Daejeon University (Daejeon, Republic of Korea). The trial period will include 4 weeks of medication (twice a day) and 2 weeks of follow-up. The study procedure is summarized in Figure 1 and Table 1. A total of 30 participants will be included and they will be randomly assigned to a SYM group or a wait-list group in a 1:1 allocation ratio. Participants will be informed about the objectives, procedures, and potential benefits, and risks of the trial through standardized interviews prior to their participation and informed consent will be obtained from all participants. Participants will be allowed to withdraw from the study at any time without negative consequences and will be immediately notified when new information regarding the study is obtained. The personal information of the participants will be de-identified and will be accessible only to the investigators involved in this study. This follows the Consolidated Standards of Reporting Trials (CONSORT) Extension for Chinese Herbal Medicine Formulas 2017^[21]^ and Standard Protocol Items: Recommendations for Interventional Trials (SPIRIT) 2013 statement.^[22]^ In addition, the trial will be conducted in accordance with the Declaration of Helsinki and Good Clinical Practice Guidelines.

**Figure 1 F1:**
[figure not shown]
Flow diagram of the trial.

**Table 1 T1:**
[figure not shown]
Schedule of enrolment, interventions, and assessments.

### Recruitment

2.2

Participants will be recruited through offline and online recruitment notices, including posters and webpages. Screening will continue until 30 participants have been enrolled. The estimated recruitment period is from June 2020 to May 2021.

### Inclusion criteria

2.3

1.adults aged 19 years or over but under 80 years;2.fulfillment of the DSM-5 diagnostic criteria for insomnia disorder^[1]^;3.total Insomnia Severity Index (ISI) score ≥15 points;4.patients with prehypertension (systolic blood pressure [SBP] 120 to 139 mm Hg or diastolic blood pressure [DBP] 80 to 89 mm Hg) or stage 1 hypertension (SBP 140–159 mm Hg or DBP 90–99 mm Hg), as defined in the seventh report of the joint national committee^[20]^;5.have voluntarily signed written informed consent forms approved by the institutional review board (IRB) after sufficient explanation about this study.

### Exclusion criteria

2.4

1.started taking sleep medication to improve insomnia or changed the type or dosage of a regularly taken sleep medication within 2 weeks prior to screening;2.have taken herbal medicine to improve insomnia within 2 weeks prior to screening or have plan to take it to improve insomnia during the study period;3.started Korean medicine treatment besides herbal medicine (acupuncture, moxibustion, or cupping therapy), dietary supplements, or other non-pharmacological therapies for the purpose of improving insomnia within 2 weeks prior to screening;4.diagnosed with sleep disorders besides insomnia such as sleep-related breathing disorder, hypersomnia, circadian rhythm sleep disorder, restless leg syndrome, and periodic limb motor disorder;5.working shifts or changes in day/night work schedule that can impact on circadian rhythm;6.diagnosed with major depressive disorder, anxiety disorder, panic disorder, or other psychiatric disorders or a Patient Health Questionnaire-9 score ≥ 10;7.have sleep disturbance caused by any type of pain;8.uncontrolled thyroid function (abnormal level of free thyroxine (free T4) and thyroid-stimulating hormone (TSH) < 0.1 μIU/ml or TSH > 5.1 μIU/ml);9.have received antihypertensives, Korean medicine treatment (acupuncture, moxibustion, cupping therapy, or herbal medicine), dietary supplement, or other non-pharmacological therapies for the purpose of controlling blood pressure within 4 weeks prior to screening;10.a history of aortic constriction, hyperaldosteroneemia, renal artery stenosis, Cushing's disease, chromophiloma, or polycystic kidney disease suspected of secondary hypertension;11.a history of asthma, chronic obstructive pulmonary disease, cerebrovascular disease (stroke, transient ischemic attack), cardiovascular disease (myocardial infarction, angina pectoris, heart failure, valve disease), malignant tumors, and active tuberculosis within 6 months prior to screening;12.uncontrolled diabetes mellitus with HbA1c ≥ 9% or fasting blood glucose ≥160 mg/dl;13.women who are pregnant or lactating, or women who do not agree to use effective methods of contraception during the clinical trial;14.severe liver or renal disease (aspartate aminotransferase (AST) or alanine aminotransferase (ALT) levels ≥5 times the upper limit of normal or creatinine levels ≥2 times the upper limit of normal);15.a history of alcohol or drug abuse;16.genetic problems of galactose intolerance, Lapp lactase deficiency, or glucose-galactose malabsorption;17.less than 1 month from the end of the intervention in a previous clinical trial;18.judged to be unsuitable for participation in this clinical trial for other reasons.

### Randomization and allocation concealment

2.5

A statistician independent of the intervention and evaluation procedures used in the clinical trial will generate random allocation numbers using the statistical program R version 3.6.1 (The R Project for Statistical Computing), with a 1:1 allocation ratio for the SYM group and wait-list group. Participant assignment in this clinical trial will be based on a block randomization method without stratification. Block sizes 2, 3, 5, and 6 will be randomly selected and a sequence that can be assigned to each block size will be randomly selected. This process will be repeated until the target number of participants is reached. The statistician will seal the randomization codes in sequentially numbered opaque envelopes and these envelopes will be kept in double-locked cabinets. Each envelope will be opened by investigators to assign the enrolled participant to the SYM or wait-list group.

### Blinding

2.6

Due to the study design, the SYM group and the wait-list group, the blinding of participants and prescribing personnel is not possible. However, blinding of the outcome assessors will be maintained during the study period by separating the researchers who will prescribe and explain the investigational product from those who will measure the outcomes. In addition, the statistician who will analyze the results will be blinded to group allocation.

### Interventions

2.7

Participants in the SYM group will receive 3.0 g SYM granules twice a day before or between meals for 4 weeks. The dosage is based on the regimen approved by the Korea Ministry of Food and Drug Safety. We will use Kracie Sihogayonggolmoryeo-tang Extract Fine Granules manufactured by Kracie Pharma Korea Co., Ltd (Seoul, Republic of Korea) in accordance with good manufacturing practice standards. The SYM granule is a light brown-brown mixture of the hot water extracts of 11 medicinal plants: *Bupleuri Radix* 5.0 g, *Fossilia Ossis Mastodi* 2.5 g, *Ostreae Testa* 2.5 g, *Scutellariae Radix* 2.5 g, *Cinnamomi Ramulus* 3.0 g*, Poria Sclerotium* 3.0 g*, Zingiberis Rhizoma Recens* 0.8 g, *Zizyphi Fructus* 2.5 g*, Rhei Radix et Rhizoma* 1.0 g*, Pinelliae Tuber* 4.0 g, and *Ginseng Radix* 2.5 g per 1 day. A pharmacist will be responsible for the storage, dispensation, and quality control of the SYM granules. If there are any adverse events during the study period, investigators will take appropriate action depending on the severity of the adverse event and the causal relationship with the investigational product.

The wait-list group will not receive SYM granules and will be instructed to maintain conventional care during the study period. The participants in this group will receive 2 weeks of SYM granules as compensatory treatment after the wait-list period if desired under the judgment of Korean medicine doctors, although this will not be included in the analysis. All participants in both groups will be educated and provided with brochures on maintaining sleep hygiene and hypertension lifestyle modification including diet and exercise during the study period.

Concomitant administration of drugs that are judged by the investigator to have no effects on the interpretation of the results of this clinical trial will be permitted. Sleep medication taken regularly from 2 weeks prior to trial participation will be permitted only if the type and dose of the drug are not changed during the clinical trial period. In addition, participants receiving Korean medicine treatment besides herbal medicine, dietary supplements, or other non-pharmacological therapy for the purpose of improving insomnia from 2 weeks prior to trial participation will be permitted if the regimen is not changed during the trial period. However, the administration of herbal medicine for the purpose of improving insomnia will be prohibited during the study period. Participants will be instructed not to change the dose or type of allowed concomitant medications at the screening visit if possible and the investigators will record the details of any changes in case report forms (CRFs).

The use of antihypertensive drugs, central nervous system stimulants, antidepressants, oral steroids, oral contraceptives, and appetite suppressants that can affect sleep or blood pressure will be prohibited during the study period. However, for oral steroids, prednisone or equivalent corticosteroids will be allowed if taken for less than 30 days at a dose less than 0.25 mg/kg/day, which is not considered to affect sleep or blood pressure.^[23,24]^

### Outcome measures

2.8

#### Primary outcomes

2.8.1

The primary outcome measure is the total ISI score and will be measured at all visits. The primary endpoint is 4 weeks after treatment. The ISI questionnaire is designed to screen for the diagnosis and severity of insomnia through 7 items corresponding to the symptoms of insomnia. The total score ranges from 0 to 28, with 0–7 indicating no clinically significant insomnia, 8–14 indicating subthreshold insomnia, 15–21 indicating clinical insomnia (moderate severity), and 22–28 indicating clinical insomnia (severe). We will use the validated Korean version of the ISI questionnaire in this study.^[25,26]^

#### Secondary outcomes

2.8.2

Sleep quality will be measured using the Pittsburgh Sleep Quality Index (PSQI) questionnaire. The PSQI evaluates 7 items including subjective sleep quality, sleep latency, sleep duration, habitual sleep efficiency, sleep disturbances, use of sleep medication, and daytime dysfunction during the past month. A total PSQI score >5 indicates poor sleep quality.^[27]^ The validated Korean version of the PSQI questionnaire will be measured at all visits except for the screening visit.^[28]^ The participants self-reported sleep diary will be collected from 1 week before medication to the end of the trial. The sleep diary will include sleep information such as the bedtime at the previous night, waking time in the morning, sleep latency, and the number and duration of wake times after sleep onset. Sleep diary-derived sleep efficiency will be calculated as (total sleep time/total time in bed X 100%).^[29]^ We will compare the average of sleep parameters contained in the sleep diary during 1 week before each visit.

SBP and DBP will be measured using an automatic blood pressure meter (FT-700R, Jawon Medical Co., Republic of Korea). Blood pressure will be measured at every visit and participants will be instructed not to smoke, drink alcohol, or consume caffeine-containing beverages within 30 minutes before the measurement. At each time point, the participants will be allowed to rest for at least 5 minutes before the first blood pressure measurement. At the screening visit, the blood pressure in both arms will be measured consecutively and the arm with the higher blood pressure level will be measured twice at 1–2-minute intervals. Arms measured consecutively at the screening visit will be continuously measured at other visits, and the average of 3 measurements per visit will be used as an outcome measure. To evaluate the degree of atherosclerosis, the degree of arterial stiffness and stenosis will be assessed noninvasively through the brachial-ankle pulse wave velocity (baPWV) and the ankle-brachial index (ABI) using VP-1000plus (OMRON Healthcare Co., Kyoto, Japan) at all visits except the screening visit.^[30,31]^ In addition, atherosclerosis biomarkers including high-sensitivity C-reactive protein (hs-CRP), erythrocyte sedimentation rate (ESR), homocysteine, and fibrinogen will be measured at the screening visit and 4 weeks after randomization.^[32–35]^

The anxiety and depression levels of participants before and after treatment will be measured using the Korean version of the hospital anxiety and depression scale (HADS) questionnaire.^[36]^ This questionnaire contains 14 items consisting of an odd 7 anxiety subscale and an even 7 depressive subscale, assessed on a 4-point scale (0 to 3). It will be measured at all visits except the screening visit. The health-related quality of life will be measured using the Korean version of the 5-level EuroQol-5 dimensions (EQ-5D-5L).^[37,38]^ This is a self-report questionnaire that evaluates 5 domains including mobility, self-care, usual activities, pain/discomfort, and anxiety/depression using a 5-point scale (1 to 5). The health status will be evaluated using the EuroQoL visual analogue scale (EQ-VAS) drawn with 0–100 vertical lines. In addition, the participants subjective perception of overall improvement after treatment will be assessed using the patient global impression of change (PGIC) questionnaire assessed with a 7-point Likert scale, ranging from “very much worse” to “very much improved”.^[39]^ The time points for each outcome measure are presented in detail in Table 1.

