## Discussion

3

This is a study protocol for a randomized, wait-list controlled, parallel, pilot clinical trial evaluating the effect of SYM on patients with both insomnia disorder and prehypertension or stage 1 hypertension. We will evaluate the preliminary effectiveness and safety of 4-week administration of SYM compared to lifestyle modification only and assess the feasibility of large-scale randomized controlled trials.

Insomnia and high blood pressure are very common diseases worldwide, and the economic burden is substantial.^[2,41]^ In particular, the 2 diseases have been reported to be associated with each other.^[5–8]^ For patients with prehypertension or stage 1 hypertension in particular, active lifestyle modification is recommended before medication.^[19,20]^ If patients with insomnia disorders and prehypertension or stage 1 hypertension taking sleep sedatives have elevated blood pressure and therefore take antihypertensive drugs, there may be risks associated with the combination of multiple drugs. However, there is no recommended conventional medication for treating both insomnia and hypertension.

Herbal medicine contains multiple active components that act on multiple targets and therefore has the potential to overcome the limitations of conventional medication with a single active constituent.^[12]^ SYM is an herbal formula that has been approved by the Korea Ministry of Food and Drug Safety and is commercially marketed for symptoms that accompany hypertension (insomnia, anxiety, and palpitation), nervousness, and morbid night crying of babies. Because SYM is an herbal medicine that is already used for treating patients with insomnia disorder and hypertension, the effectiveness and safety have been proven in historical medical literature with long-term empirical evidence. Our study will provide scientific evidence for the effectiveness and safety of SYM through a clinical trial in accordance with scientific procedures. In addition, SYM can be expected to improve not only insomnia but also blood pressure, which may reduce the risk of polypharmacy in the future.

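### The PSQI total includes a sleep-medication item, and the plan does not say whether the study granules count in it; if they do, the SYM arm's score can rise for reasons unrelated to sleep

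*Protocol article*

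**What the plan says.** Section 2.8.2 of the Protocol article measures sleep quality with the PSQI. It lists seven items, among them "habitual sleep efficiency, sleep disturbances, use of sleep medication, and daytime dysfunction during the past month". The direction of the score follows from the cut-off: "A total PSQI score >5 indicates poor sleep quality". The questionnaire "will be measured at all visits except for the screening visit", and the Methods paragraph of the abstract gives the schedule: "Data will be collected at baseline and at 2, 4, and 6 weeks after allocation".

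Section 2.7 sets the exposure in each arm. For the treated arm: "Participants in the SYM group will receive 3.0 g SYM granules twice a day before or between meals for 4 weeks". For the control arm: "The wait-list group will not receive SYM granules and will be instructed to maintain conventional care during the study period". Section 2.6 says that participants cannot be blinded, and the Discussion explains that a placebo granule could not be made. The Discussion also describes the product as "commercially marketed for symptoms that accompany hypertension (insomnia, anxiety, and palpitation" and other complaints.

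Background sleep drugs may continue in either arm if kept stable. The rule begins "Sleep medication taken regularly from 2 weeks prior to trial participation will be permitted only if the type and dose of the drug are not" and goes on to rule out alterations while the trial runs. The same section bans other herbal medicine taken for insomnia. The article nowhere links either rule to how the PSQI item is answered or scored.

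**The concern.** One of the seven scored items asks about something the randomisation itself changes. From allocation to week 4, SYM participants knowingly take a product for insomnia every day. Wait-list participants have no study product to report; the granules they may receive later come after the wait-list period and are outside the analysis. If a SYM participant treats the granules as sleep medication, the item rises from baseline whatever happens to sleep, and the total rises with it.

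The between-group PSQI difference could then understate a real benefit, or the PSQI could disagree with the ISI because of scoring rather than sleep. If some SYM participants count the granules and others do not, the mixture also adds variance in one arm of 15. This matters for a pilot whose stated use is to prepare a confirmatory trial: a distorted PSQI result could mislead the choice of outcomes and the effect size carried forward.

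**Working it through.** **Inputs from the document**
- Seven PSQI items, one on medication use, past-month recall, higher total worse (2.8.2).
- PSQI at baseline and at weeks 2, 4 and 6 (abstract and 2.8.2).
- SYM daily for 4 weeks in one arm, nothing in the other, no placebo (2.7, Discussion).
- 15 participants per arm. This reproduces section 2.9: 12 / (1 − 0.20) = 15, so 30 in total. The plan gives no PSQI figure to reproduce.

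**Assumptions, not in the document**
- The medication item scores 0 to 3, and daily use scores 3.
- q = share of SYM participants who count the granules, varied from 0 to 1.
- m = share already at the item's maximum through permitted stable sleep drugs, varied from 0 to 1. Those not at the maximum are taken to start at 0.
- For the test illustration: SD of PSQI change 3 (range 2.5 to 3.5), two-sided level 0.05.

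**Step 1: size of the shift at week 4.** Shift in the SYM arm's mean = 3 × q × (1 − m).

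| q | m = 0 | m = 0.25 | m = 0.5 | m = 1 |
|---|---|---|---|---|
| 0 | 0 | 0 | 0 | 0 |
| 0.25 | 0.75 | 0.56 | 0.38 | 0 |
| 0.5 | 1.50 | 1.12 | 0.75 | 0 |
| 1 | 3.00 | 2.25 | 1.50 | 0 |

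For one participant the largest rise is 3 points, to be read against a cut-off of 5 for the whole scale.

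**Step 2: timing.** The item covers about four weeks. The week 4 form covers essentially the treatment period. The week 2 form mixes about two untreated weeks with two treated weeks. The week 6 form mixes two treated weeks with two weeks after treatment. The table is therefore the week 4 case, and the shift is diluted at the other two visits. By how much depends on scoring thresholds that the article does not give.

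**Step 3: what such a shift would do to a test.** Two-sample t test, 15 per arm, SD 3. Standard error = 3 × √(2/15) = 1.095, so shifts of 0.75, 1.5 and 3.0 points are 0.68, 1.37 and 2.74 standard errors. From the noncentral t distribution with 28 degrees of freedom:

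| Shift | Significant result against SYM, no true effect | Power for an assumed true 3-point benefit |
|---|---|---|
| 0 | 2.5% | 75% |
| 0.75 | 9.7% | 51% |
| 1.5 | 26% | 26% |
| 3.0 | 75% | 2.5% |

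For a 1.5-point shift with no true effect, the chance of a significant result against SYM is 36% if the SD is 2.5 and 20% if it is 3.5. These figures hold the SD constant. If only some participants count the granules, the SYM arm's variance also rises, which lowers the middle rows slightly.

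**Step 4: after the fix.** If no participant counts the granules, q = 0 and the shift is 0. If the item is left out of the total, the shift is 0 whatever q is.

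**The case against.** The strongest reply is that nothing in the article says SYM is scored as sleep medication. Its vocabulary points the other way: the exclusion criteria (2.4) and the concomitant-treatment rules (2.7) handle sleep medication and herbal medicine for insomnia separately. Instructions for single questionnaire items usually sit in a full protocol or manual, and neither is shown. Every number that sets the size of the shift is assumed. The PSQI is secondary, the sleep diary gives separate sleep measures, no formal sample size rests on it, and the artefact cannot create a false benefit for SYM.

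Much of this stands. A reader might infer that scoring the PSQI as written worsens the treated arm by construction, or that the item carries assignment and not sleep quality. The document supports neither, because the shift arises only if the granules are counted, and it is nil for anyone already at the item's maximum. Nor can one say that the item could otherwise never move: 2.7 asks participants to keep allowed drugs unchanged where possible and provides for recording changes, so background use may change in either arm.

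Two parts do not dispose of the point. The separate rules for herbal and sleep medicines govern eligibility and concomitant treatment and are addressed to investigators, whereas the PSQI is answered by participants who know they are taking a product for insomnia. And the issue is more than an omitted detail: the article itself fixes the score, its items and its timing, and pairs that unmodified score with an open design without placebo. The validated Korean version does not settle whether this trial's product belongs in the item.

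**Conclusion.** The point holds as a possible bias in one secondary outcome. SYM participants who count the granules in the sleep-medication item will have a higher PSQI total unrelated to sleep quality, and wait-list participants have no such product to count. The shift in the SYM arm's mean lies between 0 and +3 points, always against SYM and greatest at week 4. This range rests on an assumed 0 to 3 item score. Where in the range the trial would fall depends on two shares the document does not give: those who count the granules and those already at the item's maximum. The test figures also need the assumed SD and significance level; they show what would follow if the granules were counted, not that they will be. The primary outcome, the ISI, is unaffected: section 2.8.1 describes its items as symptoms of insomnia. This is a cheap improvement, not a flaw that threatens the trial's main result.

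**What to change.** In section 2.8.2, state that the study product is not counted in the PSQI item on use of sleep medication. Give this instruction in the same words, in both arms, at every PSQI administration. In addition, report the PSQI total over the six remaining items as a sensitivity analysis, because some participants may count the granules despite the instruction.

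The cost is one sentence of instruction and one derived score from data already collected. The small downside is that the six-item total is not the validated total and the cut-off of 5 does not carry over to it. It should therefore support the full total, not replace it.
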